#### Secondary outcome measurements

The secondary outcome measurements are mainly related to rehabilitation after the TKA operation. They include the following.

The knee score of patients will be measured at three time points—the day before operation and on the third and tenth days after the operation—using the Hospital for Special Surgery Knee Score (HSS), commonly used in similar studies. The HSS gives a maximum of 100 points and includes pain (30 points), function (22 points), range of motion (18 points), muscular strength (10 points), deformity (10 points), instability (10 points), and subtractions (three items) [33, 34].

Active and passive range of motion (ROM) of knee joint will be measured by a standard joint protractor measure [35] on the day before the operation and the third, fifth, seventh, and tenth days after the operation.

Based on the ratio of knee circumference on the first day after the operation, the improvement of swelling around the knee joint will be evaluated on the third, fifth, seventh, and tenth days after the operation according to the following formula: (COK on the Xth-COK on the first day after operation) /(COK on first day after operation), where COK is the circumference of the knee at suprapatellar pole20 [20].

The Hamilton Anxiety Scale (HAMA) consists of 14 items, each of which has five levels [36]. In this study, the severity of anxiety in patients will be assessed on the day before the operation, and the third and tenth days after the operation.

### Assessment of the subject blinding success rate for acupuncture

Patients of the three groups will be asked to guess their assigned group to assess the masking effectiveness of the trial (Table 2), at 5 min after the end of the third treatment. Subjects will be asked the following questions: (1) How does the needle sensation feel (sensations induced by acupuncture, like sourness, numbness, distending, heaviness, etc.)? Please ring a number between 0 (no needle sensation) and 10 (unbearable needle sensation). (2) Have you ever received acupuncture? (3) Have you ever received electroacupuncture? (4) Do you think you have been treated at acupoints? (5) Are you sure you are receiving acupuncture treatment? [37] (6) At which lower extremity do you think you have been needled?

**Table 2 Tab2:**
[figure not shown]
Blind method assessment questionnaire

Note: The questionnaire survey will be completed within 5 min after the end of the third treatment

### EA safety and adverse events

Although acupuncture has been deemed a safe and reliable therapy, its adverse effects and complications associated should raise concerns [12]. Clinically, the incidence of minor adverse events related to acupuncture may be higher, such as pain, local infection, fatigue, local hematoma, subcutaneous hemorrhage, etc. [38, 39]. Some of these might be avoidable [40]. During the treatment period, acupuncturists will strictly abide by the operating rules of electroacupuncture [41]. All acupoints are around the knee joint(s). Acupuncture insertion is in the superficial or subcutaneous regions. Occasionally, there will be a small amount of bleeding or bruising. The bleeding can be arrested by pressing with sterile cotton swabs or cotton balls. The bruising usually disappears within 2–3 days [32].

In this study, during the entire clinical trial, observers who are also blinded to group allocation will record the adverse events (AEs) related to acupuncture treatment in detail and enumerate the incidences. AEs will be managed by acupuncturists and relevant clinical experts within 24 h. Any adverse event, whether related to treatment or not, is reported by the participants and practitioners at every visit.

### Ethics and dissemination

The protocol of this clinical trial adheres to the SPIRIT guidelines. Willingness to be randomly assigned and understanding and signing the informed consent is imperative for every participant in the study. All study participants will agree in writing, and researchers will provide information on this trial in detail to each person. The ethical validity of the study has been assessed and approved by the Institutional Review Board of Guanghua Hospital, Shanghai University of Traditional Chinese Medicine (No.2018-K − 18). The study is registered in the Chinese Clinical Trials Registry (trial registration number ChiCTR1800020297), where the website will present the result of the study.

### Statistical analysis

The data in this study will be analyzed using the Statistical Package for Social Science software (SPSS version 22.0, IBM Corp, New York). After data collection, statistical analysis will be performed by a special statistician. Data analysis will be based on the intention-to-treat (ITT) principle [42], considering significance levels < 0.05 as statistically significant.

Continuous data will be represented by mean, standard deviation, median, and interquartile ranges and the categorical data by percentages.

According to whether the data are normally distributed, the analysis of baseline will be performed using a *t*-test or a Wilcoxon rank sum test for continuous data and a chi-squared test or Fisher’s exact test for categorical data. Comparisons among the three groups will be analyzed by one-way analysis of variance (ANOVA) [43]. When the distribution is not normal, nonparametric tests will be used. Thus, the primary outcome will be assessed using a one-way, repeated-measures ANOVA to test the influence of the time, the group, and the time*group interaction on pain. Comparisons of categorical data among groups will be tested by the chi-square test or the Mann Whitney U-test.

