**Methods/design:**

This is a protocol for a randomized controlled patient- and assessor-blinded trial with three parallel arms (A, opposing EA; B, operated side EA; C, sham EA). *Yinlingquan* (SP9), *Yanglingquan* (GB34), *Futu* (ST32), and *Zusanli* (ST36) acupoints are selected for all three groups. In group A, the healthy side will be treated with EA, while the operated side will be administered sham EA. In group B, the operated side will be treated with EA while on the healthy side sham EA will be used. For group C, sham EA will be used on both sides. All patients in the three groups will receive treatment once a day for 3 days. The post-operative pain measured using a visual analogue scale score (including pain while resting and being active) and the additional dose of the patient-controlled analgesic pump after operation will be recorded as the primary outcomes. Secondary outcomes such as knee function and swelling, range of motion (including active and passive range of motion), post-operative anxiety, and acupuncture tolerance will also be assessed.

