## Methods/design

### Objective

The aim of this study is to investigate the effectiveness of opposing EA compared with operated side EA or sham EA treatment in patients after unilateral TKA, and to provide clinical evidence for the treatment of post-operative pain by opposing needling.

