### Study design

A randomized, controlled, three-arm, patient- and assessor-blinded trial will be conducted to compare the efficacy of two true EA groups (opposing EA and operated side EA) with a sham EA group (Fig. 1).

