### Outcome measures

#### Primary outcome measurement

The main evaluation criterion is pain, which is divided into two parts.

The first part is a visual analogue scale (VAS). The assessment schedule is shown in Table 1. Independent assessors who are not involved in acupuncture treatments will perform the VAS assessments (asking subjects to indicate the intensity of pain at the most painful points while resting and walking). The 0–100 mm VAS is used to evaluate pain intensity, wherein 0 mm denotes painless and 100 mm represents the most intolerable pain [32]. It allows patients to mark their own feelings on the scale as the evaluation score of pain. In addition to evaluating resting pain at 6 h after the operation, the pain in both the resting and active state is measured immediately after treatment on the first to third days after the operation, and assessed at follow-up on the fifth, seventh, and tenth days after the operation.

**Table 1 Tab1:** Schedule of trial enrollment, interventions, and assessments

Items	Enrollment (pre-operative)	Allocation (baseline)	Treatment (post-operative)				Follow-up		
Time point (hour/day)	-1	-1	6 h	1d	2d	3d	5d	7d	10d
Treatment sessions (n)	–	–		1	2	3			
Informed consent	√								
Assessment of eligibility	√								
VAS (resting)		√	√	√	√	√	√	√	√
VAS (active)		√		√	√	√	√	√	√
Additional dose released by PCA pump					√				
HSS score		√				√			√
HAMA score		√				√			√
AROM		√				√	√	√	√
PROM		√				√	√	√	√
COK				√		√	√	√	√
Discomfort and acceptance of EA				√	√	√			
Assessment of blinding method						√			
Postoperative complications and adverse events				√	√	√			

*VAS* Visual Analogue Score, *PCA* patient controlled analgesia, *HSS* hospital for special surgery, *HAMA* Hamilton Anxiety Scale, *COK* circumference of knee, *AROM* active range of motion, *PROM* passive range of motion

The second part is to record any additional doses from the patient-controlled analgesic pump after the operation, and to evaluate it uniformly on the second day after the operation (at 24 h after the first treatment).

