### Sample size

According to the data from the previous preliminary study, through observing the analgesic effect of opposing EA three times after TKA operation, the average VAS score was 37.0 with a standard deviation = 22.6, the average value of sham EA was 46.9, and the standard deviation was 12.5, with a significance level α = 0.05 (two-sided) and power (1 − β) = 0.8. According to the following sample size formula [44, 45], μ is the mean and σ is the standard deviation, κ = n_A_/n_B_ is the matching ratio. τ is the number of comparisons to be made. Look-up table Ζ can be obtained. The sample size was calculated as 96 cases; taking a 15% dropout rate into account, 38 subjects are required in each of the three groups.
$$ {n}_A=\left({\sigma}_A^2+{\sigma}_B^2/\upkappa \right){\left(\frac{Z_{1-\alpha /\tau }+{Z}_{1-\beta }}{\mu_A-{\mu}_B}\right)}^2 $$

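### Three unranked primary outcomes and two different sets of arm contrasts share one 0.05 level, with no rule on which result decides the trial

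*Protocol article*

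**What the plan says.** **Outcomes.** The Abstract (Methods/design) lists post-operative VAS pain, "including pain while resting and being active) and the additional dose of the patient-controlled analgesic pump after operation will be recorded as the primary outcomes". The Primary outcome measurement section agrees: "The main evaluation criterion is pain, which is divided into two parts". That gives three variables: resting VAS, active VAS and additional PCA dose. None is placed first, and neither section says whether one success is enough or all are needed.

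**Contrasts.** The Objective is to "investigate the effectiveness of opposing EA compared with operated side EA or sham EA treatment", that is, opposing versus operated-side and opposing versus sham. The Study design section says the trial will "compare the efficacy of two true EA groups (opposing EA and operated side EA) with a sham EA group", that is, opposing versus sham and operated-side versus sham. Only opposing versus sham is in both.

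**Level and tests.** The Statistical analysis section applies one level, "considering significance levels < 0.05 as statistically significant". Comparisons among the three groups use one-way ANOVA. The primary outcome goes into a repeated-measures ANOVA with tests of time, group and their interaction.

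**Sizing.** The Sample size section works "with a significance level α = 0.05 (two-sided) and power (1 − β) = 0.8" and uses means and SDs for opposing and sham EA only. It does not say whether the VAS was resting or active. Its formula takes the normal quantile at 1 − α/τ, where "τ is the number of comparisons to be made", but τ is given no value.

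**The concern.** Several results could each be reported as the primary finding: three variables, up to three pairs of arms, and for each VAS state both a group test and an interaction test. When all are judged at 0.05 and none is named as decisive, a single significant result among them could be presented as success, and the error rate behind that statement is higher than 5%. The two descriptions of the contrasts add to this, because a reader cannot tell from the article which comparison the trial is meant to settle.

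The comparison of opposing with operated-side EA needs care for another reason. The Discussion argues that needling the healthy leg is more convenient, more acceptable and less of an infection risk. A non-significant difference could then be taken to mean that the two are equally effective, although the sample size was not built on that comparison.

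**Working it through.** **1. The plan's own figure.** Inputs from the Sample size section: means 37.0 and 46.9 (difference 9.9), SDs 22.6 and 12.5, α = 0.05, power 0.8; κ = 1 from the 1:1:1 allocation.

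n per arm = (22.6² + 12.5²) × ((Z₁₋α/τ + 0.842)/9.9)² = 667.01 × ((Z + 0.842)/9.9)²

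| τ | Z | n per arm | three arms |
|---|---|---|---|
| 1 | 1.645 | 42.1 → 43 | 129 |
| 2 | 1.960 | 53.4 → 54 | 162 |
| 3 | 2.128 | 60.02 → 61 | 183 |

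The stated 96 (32 per arm) is below all of these. Only the dropout step reproduces: 32/0.85 = 37.6 → 38 per arm, 114 in total. So the stated size shows no sign of a divided α. Also, τ = 2 gives the ordinary two-sided quantile 1.960.

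**2. Chance of at least one false positive.** The assumptions are: no true difference anywhere, normal data, 38 per arm, every test at 0.05, and a correlation r between the three primary variables. The article gives no such correlation, so r is varied from 0 to 0.7. For the repeated-measures tests, six shared VAS times (days 1, 2, 3, 5, 7, 10) and a within-patient correlation of 0.5 or 0.7 are also assumed.

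| What counts as success | r = 0 | r = 0.3 | r = 0.5 | r = 0.7 |
|---|---|---|---|---|
| 3 overall group tests, or pairwise tests only after a significant ANOVA | 14% | 14% | 13% | 11% |
| 5 tests: group and time-by-group for each VAS state, plus PCA | 23% | 22% | 21% | 19% |
| 9 ungated pairwise tests (3 variables × 3 pairs) | 32% | 31% | 29% | 25% |

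Check at r = 0: 1 − 0.95³ = 14.3% and 1 − 0.95⁵ = 22.6%. For nine tests, 1 − 0.95⁹ = 37% does not apply, because the three pairs share arms and are correlated even when the endpoints are not.

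**3. Precision of opposing versus operated-side EA.** The article gives no SD for the operated-side arm, so both values below are assumptions. Half-width of the 95% CI = 1.96 × √((22.6² + s²)/n).

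| s assumed | n = 32 | n = 38 |
|---|---|---|
| 22.6 | 11.1 mm | 10.2 mm |
| 12.5 | 8.9 mm | 8.2 mm |

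The whole assumed effect of opposing EA over sham is 9.9 mm.

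**4. Power of the one contrast that was sized.** Power = Φ(9.9/√(667.01/n) − 1.96). At n = 38: Φ(2.363 − 1.96) = 66%. At n = 32: Φ(2.168 − 1.96) = 58%.

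**The case against.** The strongest reply is that a testing order, a post-hoc method and a multiplicity adjustment usually sit in the statistical analysis plan, which is not shown, and that a journal article condenses. That is right for the mechanics, and their absence is not the point here. What stands is what the article does state: three primaries on an equal footing, two different sets of contrasts, and one level for all tests. The two contrast lists are not mutually exclusive, since together they cover all three pairs. That widens the family without saying which member decides.

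Four stronger readings are tempting and are not supported:

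- **Each visit is tested separately.** The article puts the times jointly into a repeated-measures ANOVA. The time effect itself is not a treatment comparison, so time adds at most one interaction test per VAS state.
- **The error rate is a fixed 20–30%.** It depends on which tests count. The upper figures need nine ungated pairwise tests, which the article does not name, and the middle figures need the interaction test to count as a route to success, which it does not say.
- **A correction was planned and then dropped.** The α/τ term is weak evidence for this, because τ has no value and τ = 2 is simply the two-sided quantile. What remains is that τ is undefined and has no counterpart in the Statistical analysis section.
- **An equivalence claim is planned.** No section states equivalence or non-inferiority, so the lack of a margin is not an error. The precision figures support only a caution about interpretation.

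**Conclusion.** The point holds in this form. Followed as written, the plan has no single decisive primary result, and every reading examined gives a false-positive chance above 5%: about 11–14% on the most lenient, about 19–23% when the group and interaction tests for both VAS states and the PCA test all count, and about 25–32% for nine ungated pairwise tests. These figures rest on the global null, 38 per arm, normal data and assumed endpoint correlations of 0 to 0.7. Higher correlations would lower them.

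The comparison of opposing with operated-side EA is too imprecise (half-width about 8–11 mm, operated-side SD assumed) for a non-significant result to be read as similarity. That the stated 96 cannot be reproduced is a separate matter; it is used here only to show that α was not visibly divided.

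**What to change.** Before unblinding, amend the protocol as follows:

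1. Name one primary test: opposing EA versus sham EA, the contrast that was sized, on one VAS state at one stated time or model term, two-sided 0.05. It must match the sample-size input. Resting VAS after the third session is one possibility, but the sponsor must confirm which VAS the preliminary data were.
2. Test the other VAS state, the additional PCA dose, and operated-side EA versus sham in a stated fixed order at 0.05, stopping at the first non-significant result. Treat all other times and contrasts as descriptive.
3. Report opposing versus operated-side EA as a difference with a 95% CI, and state that non-significance will not be called equivalence.
4. Align the Objective, Study design, Statistical analysis and Sample size sections with this order, and give τ a value or remove it.

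**Cost.** No extra patients. By contrast, dividing a two-sided α by three would need 72 per arm on the stated inputs, and 72/0.85 → 85 per arm with dropout (255 in total). The price of the sequence is that later steps cannot be claimed once an earlier one fails, and the first test has only about 58–66% power on the stated inputs. Opposing versus operated-side EA, although named in the Objective, becomes an estimate and not a test. The change also needs ethics committee approval, as the Data management section requires.

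### The trial is sized on opposing EA versus sham EA, but the primary VAS analysis consists of omnibus tests that do not estimate that difference and leave the collected pre-treatment VAS unused

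*Protocol article*

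**What the plan says.** **Sizing.** The Sample size section rests on two arms. For opposing EA, "the average VAS score was 37.0 with a standard deviation = 22.6"; for sham EA, "the average value of sham EA was 46.9, and the standard deviation was 12.5". It arrives at 96 evaluable patients (32 per arm), raised to 38 per arm for 15% dropout.

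**Analysis.** The Statistical analysis section gives a general rule, "Comparisons among the three groups will be analyzed by one-way analysis of variance (ANOVA"), with the fallback "When the distribution is not normal, nonparametric tests will be used". For pain it says that "the primary outcome will be assessed using a one-way, repeated-measures ANOVA to test the influence of the time, the group, and the time*group interaction". (The label one-way does not fit a model with group, time and their interaction.) No pairwise contrast is named. Baseline appears only as something to compare between arms: "the analysis of baseline will be performed using a" *t*-test or rank sum test. It is not named as a covariate.

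**Measurement times.** Table 1 lists resting VAS at day -1, 6 h and days 1, 2, 3, 5, 7 and 10 (eight times). Active VAS has the same times without 6 h (seven). The 6 h value is introduced by "In addition to evaluating resting pain at 6 h after the operation". Treatment starts on day 1, and that day's VAS is taken after the session. The additional PCA dose, the other part of the primary outcome, is evaluated once, on day 2.

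**The concern.** The quantity the trial was sized to detect is a difference between two arms. None of the three stated tests is that difference. The group test has 2 df, and a significant result does not say which arms differ. Over eight visits the time*group test has 2 x 7 = 14 df, and it can be significant for a pattern that has nothing to do with A versus C. The time test is not a treatment question. A reader of the results could be left with a p-value and no primary estimate.

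The pre-treatment visits add a second problem. No treatment effect can exist at day -1 or 6 h. If those values enter as outcomes, they dilute the group main effect. Entered as covariates, the same values would reduce the error variance.

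**Working it through.** **1. The plan's own figure.** The printed formula with kappa = 1 is n = (22.6² + 12.5²) x ((z + 0.842)/9.9)² = 6.806 x (z + 0.842)². It gives 42.1, so 43 per arm, with z = 1.645 (tau = 1); 53.4, so 54, with z = 1.960 (tau = 2); and 60.0 (rounded up, 61) with z = 2.128 (tau = 3). None of these gives the stated 32. Only the dropout step reproduces: 32/0.85 = 37.6, so 38. That is a separate matter; 32 per arm is taken as given below. Power for A versus C on a single unadjusted VAS at 32 per arm is 0.58.

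**2. Dilution, if all scheduled visits enter.** For a constant effect of 9.9 mm at the six post-treatment visits:
- resting: 9.9 x 6/8 = 7.4 mm
- active: 9.9 x 6/7 = 8.5 mm

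**3. Assumptions for power (not in the protocol).** Effect constant from day 1 to day 10; the same correlation rho between any two visits, 0.3 to 0.7; mean of the operated-side arm (B) anywhere from A to C; SD in B = 18.3, the root mean square of 22.6 and 12.5, so the pooled variance is 333.5.

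**4. Closed form at rho = 0.5, resting VAS.** S is 2/3 if B equals A or C, and 1/2 if B is midway.
- Group test (2 and 93 df): lambda = 32 x 7.425² x S / (333.5 x (1 + 7 rho)/8) = 6.27 or 4.70; power 0.59 or 0.47.
- Interaction (14 and 651 df): lambda = 32 x 9.9² x 1.5 x S / (333.5 x (1 - rho)) = 18.8 or 14.1, where 1.5 = 8 x (6/8) x (2/8); power 0.80 or 0.65.
- A versus C on the mean of six post-treatment visits, adjusted for one pre-treatment VAS: variance factor (1 + 5 rho)/6 - rho² = 0.333; SE = sqrt(667.0 x 0.333/32) = 2.64; 9.9/2.64 = 3.76; power = Phi(3.76 - 1.96) = 0.96.

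**5. Simulation (2,000 runs per scenario, 32 per arm).** Ranges run over the position of B.

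| VAS, rho | Group test | Interaction | A vs C, adjusted post-treatment mean |
|---|---|---|---|
| Resting, 0.3 | 0.63-0.79 | 0.45-0.65 | 0.95-0.96 |
| Resting, 0.5 | 0.47-0.63 | 0.65-0.83 | 0.95-0.96 |
| Resting, 0.7 | 0.38-0.51 | 0.90-0.98 | 0.99 |
| Active, 0.3 | 0.75-0.90 | 0.28-0.38 | 0.96 |
| Active, 0.5 | 0.56-0.76 | 0.39-0.55 | 0.95-0.96 |
| Active, 0.7 | 0.46-0.61 | 0.64-0.84 | 0.98-0.99 |

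With SD 22.6 in B instead, the resting group test runs at about 33-73% and the interaction at about 36-99%.

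**6. Where the gain comes from.** Without adjustment, A versus C on the resting post-treatment mean has 0.89-0.91, 0.78-0.80 and 0.69-0.70 at rho 0.3, 0.5 and 0.7. The rest of the gain is the covariate, and it depends on how well pre-treatment VAS predicts later VAS. If that correlation is only rho/2, the variance factor is (1 + 5 rho)/6 - rho²/4 and power is 0.93, 0.85 and 0.78.

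**The case against.** The strongest reply is that the protocol does not say which visits enter the ANOVA, and that visit set, covariates and contrasts are often fixed in a separate analysis plan, which is not at hand. The objective also sets opposing EA against operated-side EA as well as sham EA, so a three-arm test is not foreign to it. This stands in part. The dilution is conditional, and two pre-treatment values exist for resting VAS only. What the article does fix is the type of test for the primary outcome, and that type does not match the quantity used for sizing.

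A reader might infer more than the text supports:

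- **That the whole plan has very low power for a short-lived effect.** With an effect confined to days 1-3, the resting group main effect has only about 11-22% power. But the plan also tests time*group, which is built for that pattern and reaches about 50-99% in the same scenario. Nor is an omnibus test always weaker than the pairwise one: at a single visit with B equal to A or C, it has 0.59 against 0.58.
- **That unequal SDs (variance ratio 3.27) invalidate the planned F tests.** With equal allocation the simulated null rejection rate is 5.5% for group and 5.6% for interaction. No pooled pairwise test is specified. If one were added, A versus C would run at 3.3%, 5.0% or 7.5% for an SD in B of 22.6, 18.3 or 12.5. This bears on how the new contrast is fitted and is not a fault in the stated tests.
- **That many patients will be lost to complete-case deletion.** The protocol gives no per-visit missing rate and no handling rule, so any such percentage is assumed.
- **That the PCA dose has no usable test.** The general one-way ANOVA or nonparametric rule suits a single value; the text only needs to say so.

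**Conclusion.** The point holds as a mismatch between sizing and analysis. The trial is sized on A versus C, while the stated primary VAS tests are omnibus, give no A-minus-C estimate and do not use pre-treatment VAS. For resting VAS with an effect lasting to day 10, the group test has roughly 35-80% power and the interaction roughly 40-98%, against about 95-99% for the adjusted A-versus-C contrast. These figures rest on all scheduled visits entering the model, 32 per arm, the stated SDs, a constant 9.9 mm effect and correlation of 0.3-0.7 that also applies to the pre-treatment value. The advantage narrows if pre-treatment VAS predicts poorly, and at rho 0.7 for resting VAS the interaction test comes close to the contrast in power. Even then it does not supply the estimate. This is a worthwhile improvement at no data cost; it does not show that the planned tests are invalid.

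**What to change.** Amend the Statistical analysis section as follows.

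1. Analyse post-treatment VAS only (days 1, 2, 3, 5, 7 and 10) in a linear mixed model with group, visit and group*visit. Use pre-treatment VAS as covariate: day -1 and 6 h for resting pain, day -1 for active pain.
2. Pre-specify the opposing EA versus sham EA contrast, at a named time or average, as the primary estimate with its confidence interval. The Sample size section mentions three treatments but names neither a day nor resting or active pain, so this has to be chosen. The mean of days 1-3 is one candidate: under the assumptions above its variance factor (1 + 2 rho)/3 - rho² gives power of 0.90, 0.92 and 0.97 at rho 0.3, 0.5 and 0.7.
3. Allow the variance to differ by arm, or use a robust SE, for pairwise contrasts.
4. State that the additional PCA dose is compared by its own between-group test, outside the repeated-measures model. It has no baseline value of its own to adjust for.

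The cost is analysis wording only. Every covariate named is already in Table 1.

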**Fig. 1 Fig1:**
[figure not shown]
The flow diagram is intended to depict the passage of participants through this RCT

The study will be sequentially conducted as follows: 114 patients in Guanghua Hospital, Shanghai University of Traditional Chinese Medicine with osteoarthritis are included (surgical contraindications are excluded); after admission, unilateral TKA will be performed as scheduled. A day before the surgery, the eligible patients will be assessed at baseline and their consent will be obtained in writing. Patients will then be randomly assigned (on a 1:1:1 ratio) to the opposing EA group, the operated side EA group, or the sham EA group. Random numbers will be generated by the SPSS 22.0 software and sealed in opaque envelopes. Only the operator in charge of acupuncture treatment is authorized to open the envelope to obtain the group code.

The three groups of subjects will receive interventions on three consecutive days after surgery, once every day, by a clinician with more than 3 years of experience in acupuncture intervention. The participants will be blinded to the intervention measures. The success of the visit would be evaluated during the last visit of each participant. Researchers who did not participate in the treatment and who did not know the allocation results will perform the outcome assessment. Unblinding before the completion of the study will only be allowed in the case of medical emergencies or severe adverse events (SAEs).

All patients will receive the same post-operative analgesic dose with a fentanyl patient-controlled analgesic (PCA) pump (continuous infusion rate 0.25 μg/(kg·h)). Additional analgesics will be provided as per each patient’s requirements ascertained by the visual analogue scale (VAS) score > 6, and the use of analgesics will be recorded in their case report form (CRF).

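### The Mann-Whitney U-test, a two-sample rank test, is named for comparing categorical data among the groups of a three-arm trial; ordered categories need a three-group rank test

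*Protocol article*

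**What the plan says.** On design, the Study design section states: "A randomized, controlled, three-arm, patient- and assessor-blinded trial will be conducted". Allocation is 1:1:1, with 38 patients planned per arm.

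The Statistical analysis section has four elements that bear on this point:

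- Threshold: "considering significance levels < 0.05 as statistically significant".
- The three-arm comparison: "Comparisons among the three groups will be analyzed by one-way analysis of variance (ANOVA"), followed by "When the distribution is not normal, nonparametric tests will be used". The nonparametric tests are not named.
- Baseline data: a t-test or Wilcoxon rank sum test for continuous variables, and chi-square or Fisher's exact test for categorical ones.
- Categorical data: "Comparisons of categorical data among groups will be tested by the chi-square test or the Mann Whitney U-test".

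The last sentence does not list the outcomes it covers, does not say when each test applies, and does not say how a two-sample test would be used across three arms. Candidate outcomes appear elsewhere. The abstract says that "post-operative anxiety, and acupuncture tolerance will also be assessed". Table 1 schedules discomfort with and acceptance of electroacupuncture (EA) on days 1 to 3. There is also a blinding questionnaire after the third treatment, and adverse events are recorded.

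**The concern.** A comparison among three arms asks whether all three share one distribution. Mann-Whitney asks whether two samples do. With three arms it can only be applied pair by pair, which is a different procedure with its own error rate. It also needs ordered values. For an unordered answer, such as which leg the patient believes was needled, ranks carry no meaning.

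This is a named method that does not fit the design, and so differs from detail that a condensed article leaves to an analysis plan. The rest of the paragraph does not supply the right test: Kruskal-Wallis is not mentioned, and the other named rank test, the Wilcoxon rank sum, is also a two-sample test.

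At stake is the error rate for ordered supporting outcomes, and the freedom that the word *or* leaves to choose test and pairs once data are in hand.

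**Working it through.** **Inputs.** Three arms, 1:1:1, and a threshold of 0.05 per test (protocol article: Study design, Statistical analysis). Per-arm size is 96/3 = 32 before dropout and 38 after it (Sample size). The article states no error rate for the categorical tests other than 0.05, so that is the figure to reproduce first. No scale is given for the tolerance or acceptance item, so the category probabilities below are assumptions, varied to show the range.

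**Which pairs.** Study design sets each true EA arm against sham: two pairs. Objective sets opposing EA against operated-side EA or sham: also two pairs. Their union is all three pairs.

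**Theory under no difference among arms (large-sample, critical value 1.96).**

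1. One Mann-Whitney test: 0.05, as stated.
2. Two active-versus-sham tests. With equal arms sharing one control, the two z-statistics have correlation n/(n + n) = 0.5. Then 1 − P(|Z1| < 1.96 and |Z2| < 1.96) = 0.091, and 0.091/0.05 = 1.8 times nominal.
3. All three pairs. At least one pair is significant when the range of three standard normals exceeds 1.96 × √2 = 2.77. The studentized-range distribution for three groups gives 0.122, and 0.122/0.05 = 2.4 times nominal. Treating the pairs as independent would give 1 − 0.95³ = 0.143, which is too high because the pairs share arms.

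**Simulation check.** 20,000 null trials per setting, tie-corrected tests, 38 per arm:

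| Outcome (assumed probabilities) | One MW test | Two pairs vs sham | Any of three pairs | Kruskal-Wallis | Pairs only after significant Kruskal-Wallis |
|---|---|---|---|---|---|
| Binary (0.8, 0.2) | 5.1% | 9.2% | 12.2% | 4.9% | 4.9% |
| Five levels, equal (0.2 each) | 4.8% | 9.2% | 12.2% | 4.8% | 4.8% |
| Four levels, skewed (0.55, 0.25, 0.15, 0.05) | 4.8% | 8.9% | 11.9% | 4.9% | 4.9% |

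Across these shapes and a continuous one, at 32 and 38 per arm, the ranges are:

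- one test: 4.8–5.2%;
- two pairs against sham: 8.7–9.5%;
- any of three pairs: 11.9–12.8%;
- Kruskal-Wallis, alone or as a gate: 4.6–5.3%;
- three pairs each at 0.05/3: 3.9–4.6%.

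The simulation standard error is √(0.05 × 0.95/20,000) = 0.15 percentage points near 5% and √(0.12 × 0.88/20,000) = 0.23 near 12%.

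**Why the gate works with three arms.** If all three arms are equal, the overall test holds about 5%. If exactly one pair is equal, there is only one true null to reject wrongly, and it is tested at 5%. If no pair is equal, no false rejection is possible.

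**Which outcomes are reached.** VAS, PCA dose, HSS, range of motion, knee circumference ratio and HAMA are numeric or scores, and other sentences of the section cover continuous data. That leaves the acceptance item (if graded), blinding answers and adverse events.

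**The case against.** Several points on the other side are sound.

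- *The inflated rate is not in the plan.* A reader might infer that the named test more than doubles the false-positive rate. The documents do not support that as a fact. It needs all three pairs tested at unadjusted 0.05 with no overall test, and the article describes no such procedure. The two contrasts of Study design give about 9%, which is below double, and a single or gated test stays near 5%. This stands, and the rates are given here as conditional.
- *Chi-square is in the same sentence.* It tests the three-group null and suits unordered answers; the natural reading is chi-square for nominal data and a rank test for ordered data. A reader might infer that p-values for unordered answers will depend on arbitrary coding. That would require Mann-Whitney to be chosen for nominal data, which the article does not say. This also stands.
- *The aims are partly pairwise.* Objective and Study design are worded as comparisons of arms with one another, and the words *three groups* belong to the ANOVA sentence. Mann-Whitney is acceptable for one pair of arms on ordered categories. This is true, but the sentence offers it for comparisons among groups, alongside chi-square, and not as a pairwise follow-up.
- *Detail belongs in an analysis plan.* Multiplicity rules and the choice between tests may be set out there, and their absence here is no finding. A wrongly matched test that is named outright is another matter. The unnamed nonparametric fallback could include a three-group rank test, but it is tied to the ANOVA sentence and does not correct the categorical one.

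**Conclusion.** The point holds in a limited form. The article names a two-sample rank test for categorical comparisons among groups in a three-arm trial, and names no three-group rank test anywhere. For ordered categories the sentence therefore does not provide a test of the three-arm question.

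The size depends on use. Without an overall test, the chance of at least one false positive is about 12% for all three pairs and about 9% for the two active-versus-sham pairs, against about 5% for Kruskal-Wallis. These figures assume equal arms, no true difference and no adjustment; they vary little across the assumed category shapes.

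The reach is modest. The primary outcomes are outside this sentence, as are the numeric secondary measures. Whether the tolerance or acceptance item is ordered cannot be settled, because its scale is not given. Nothing in the documents shows that an efficacy conclusion rests on this sentence. It is a correction worth making because it is clear and cheap.

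**What to change.** Replace the categorical-data sentence in Statistical analysis with:

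> Ordered categorical outcomes (for example discomfort with and acceptance of EA, if graded) will be compared among the three arms by the Kruskal-Wallis test, with pairwise Mann-Whitney tests only if it is significant. Unordered and binary outcomes will be compared by the chi-square test, or by the Fisher-Freeman-Halton exact test when expected counts are small.

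State the scale of the acceptance item so that it is clear which branch applies, and settle the wording before unblinding. Testing each of the three pairs at 0.05/3 would also control the error, but is slightly conservative (3.9–4.6% in the simulation). The cost is one sentence, with no change to data collection, visits or sample size.
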